### **Follow-Up**

**The research protocol must give a clear indication of what follow up will be provided to the research participants and for how long. This may include a follow up, especially for adverse events, even after data collection for the research study is completed.**

We provide a clear protocol for each volunteer and the instruction to follow during the intervention study.

## INSTRUCTIONS FOR VOLUNTEERS:

[figure not shown]

## URINE COLLECTION

When getting up on day 3, take your urine (eg 7:00). Record this time on 'your' schedule '. Then you have to collect all your urine for 24 hours (day and night) in different urine containers. Just before the end of the 24 hours, one day later (day 4) on the same time (eg day 4 at 7:00), you catch your urine for the last time. Put an alarm clock so you do not forget about this time to urinate. After this your 24 hour urine is complete. Note the schedule always the time you have all your urine samples collects.

- You can get the urine first in the collector cup (1000 ml graduated cup).

- Then read the amount of urine and record this volume on your schedule.
- Transfer your urine into the smaller urine containers.
- Always use another container per splash.
- On your schedule, indicate which containers were used at any place.
- Keep your urine in a cool dark place in the zipper bag you received (frigo or freezer).
- Keep in mind that small amounts of urine and urine must be collected before or after the stool.
- The collector can be rinsed with hot water (no detergent) and allow to dry in the air.
- Secure a safety pin to your underwear. This reminds you to get your urine all day long catching in the container.
- To get enough urine for this study, it is important that you drink enough (2 liters of moisture) for 24 hours).

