The subjects have to follow a strict cereal-free diet during 3 days (Figure 1). Cereal-based foods and foods containing possible traces of wheat, rye, oats, maize and rice are restricted (*i.e.* bread and bread-based products, breakfast cereals, oat meal, muesli, cereal bars, waffles, cakes, (un)pealed rice, polenta, pizza, tortilla, pasta, popcorn, cereal-based chips, maize, beer, wine, pan meal and sauce-binders). The subjects are asked to detail their daily food intake through a questionnaire. On the third day in the morning, the subjects receive an oral bolus of DON or DON-3-glucoside based on the TDI ( $1\text{ }\mu\text{g/kg}$  body weight) and their body weight. The volunteers did the study twice: 1) DON administration and 2) DON-3-glucoside administration, between the two mycotoxin administration there are a washout period of two months. In addition, a control group of 4 volunteers follow the same protocol, however do not receive a bolus of DON or DON-3-glucoside after the cereal-free diet.

At day 3, volunteers have to collect a urine sample before the administration of the DON or DON-3-glucoside bolus (Figure 1). From the moment of administration, the 24-hours urine sample collection is requested. We deliver to each volunteer 12 containers (1L) to collect the urine. For every sampling point, time (hour of urine collection) and voided volume is recorded. All samples will be individually aliquotted to 20 mL, and stored in the freezer at  $-20^{\circ}\text{C}$  upon analysis. The samples are analysed with a Waters Acquity UPLC system coupled to a Quattro XEVO TQS mass spectrometer (Waters, Manchester, UK) was used to analyse the urine samples. Data acquisition and processing is performed with MassLynx™ version 4.1 and

QuanLynx® version 4.1 software (Waters, Manchester, UK). A Waters Acquity UPLC® HSS T3 (2.1 x 100 mm, 1.8 µm) column is applied (Waters, Manchester, UK).

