### **Data Management and Statistical Analysis**

**The protocol should provide information on how the data will be managed, including data handling and coding for computer analysis, monitoring and verification. The statistical methods proposed to be used for the analysis of data should be clearly outlined, including reasons for the sample size selected, power of the study, level of significance to be used, procedures for accounting for any missing or spurious data etc. For projects involving qualitative approaches, specify in sufficient detail how the data will be analysed.**

Firstly, we agree a coding system for the samples. The coding system is that all samples have two number separated by a "." where the first number is the volunteer id and the second number is the number of the sample of each volunteer. So the first urine sample of the volunteer 1 is 1.1 and the second sample of the volunteer 1 was 1.2. On the other hand, the second sample for the volunteer 2 is 2.1 and the second samples of the volunteer 2 is 2.2. We introduce an excel file all the information for each volunteer id.

Once we analyse the samples, the data of each sample is introduced in the same excel file and the results of each mycotoxin are introduced separately. Then, all obtained results are carried out on molar basis taking the molecular weight of the analytes (DON, 296 g/mole; DON-3-glucoside, 458 g/mole; DON-3-glucuronide and DON-15-glucuronide, 472 g/mole; DOM-1, 280 g/mole; 3-ADON and 15-ADON, 338 g/mole) and the total volume of each sampling point into account. Associations between independent and dependent variables are assessed by using univariate and multivariable linear regression models. Independent variables include age (years), gender, body mass index (BMI),

and the consumption of coffee. The statistical analysis is performed using the software Microsoft Excel® 2010 and SPSS® 15.0.

The excretion profiles are based in values obtained each hour after the bolus administration from a varying number of volunteers per time period. For instance, results from 61 to 120 minutes are clustered in the second hour.

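### The volunteer instructions run the 24-h urine collection from the waking void, the Study Design runs it from the bolus, so collection as instructed falls short of 24 h after dosing by the unstated gap between the two

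*Protocol*

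**What the plan says.** Three parts of the protocol set the time axis.

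- **Study Design**, repeated in the Project summary: "From the moment of administration, the 24-hours urine sample collection is requested". The same section gives the order of events: "volunteers have to collect a urine sample before the administration of the DON or DON-3-glucoside bolus". The only timing of the dose in the readable text is "On the third day in the morning, the subjects receive an oral bolus".
- **Data Management and Statistical Analysis**: "The excretion profiles are based in values obtained each hour after the bolus administration". The example given there puts minutes 61 to 120 in the second hour, so the bins are one hour wide and start at the bolus.
- **Urine Collection**, in the instructions for volunteers: "When getting up on day 3, take your urine (eg 7:00"; "Then you have to collect all your urine for 24 hours (day and night) in different urine containers"; the end is "one day later (day 4) on the same time (eg day 4 at 7:00), you catch your urine for the last time"; and then "After this your 24 hour urine is complete". The bolus does not appear in this section.

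The Study Design and Methodology sections list what is recorded for each sample: code, hour and volume.

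**The concern.** The first two sources start the 24 h at the bolus. The third, which volunteers act on, starts and ends it at the waking void. The windows coincide only if the bolus is taken at the moment of the waking void. Otherwise collection stops before 24 h have passed since dosing, and any urine passed between waking and dosing lies inside the volunteer's 24 h although it is pre-dose.

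The aims are the excretion pattern and the absorption and excretion rates. The Expected Outcomes section adds whether a morning urine or a 24-h collection is the better measure of exposure. These use the 24-h total and the time since dose. The Problems Anticipated section makes a volunteer who misses one sample start again, so the protocol itself treats a complete collection as essential. If g varies, the total covers a different length of time in different volunteers, and possibly in the same volunteer under DON and under DON-3-glucoside.

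**Working it through.** **Inputs from the protocol.** Stated collection length: 24 h from the bolus (Study Design). Instructed window: waking void at clock time T on day 3 to T + 24 h on day 4 (Urine Collection). Order: urine first, bolus second (Study Design). Bin width: 1 h from the bolus (Data Management and Statistical Analysis).

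**Inputs assumed.** The gap g is not in the readable text; 0 to 3 h is used. The Rationale calls the excretion half-life short but gives no figure; 2 to 8 h is used.

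**Step 1: reproduce the stated 24 h.** With the bolus at T + g and the last void at T + 24, post-bolus collection = (T + 24) − (T + g) = 24 − g hours. This equals the stated 24 h only at g = 0.

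| g (h) | Post-bolus hours | Shortfall, g/24 | Last complete hourly bin |
|---|---|---|---|
| 0 | 24 | 0% | 24 |
| 0.5 | 23.5 | 2.1% | 23 |
| 1 | 23 | 4.2% | 23 |
| 2 | 22 | 8.3% | 22 |
| 3 | 21 | 12.5% | 21 |

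**Step 2: share of the excreted amount that is missed.** Under first-order excretion with half-life h and no uptake phase, the share of the final urinary amount passed between 24 − g and 24 h is

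2^(−(24 − g)/h) − 2^(−24/h).

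For g = 3 and h = 8: 2^(−2.625) − 2^(−3) = 0.1621 − 0.1250 = 0.0371, or 3.71%.

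An uptake phase with rate ka delays excretion. With k = ln 2 / h, and because the uptake term has vanished by 21 h, the share is multiplied by ka/(ka − k). With an assumed ka = 1.5 per hour and h = 8, k = 0.0866 and the factor is 1.5/1.4134 = 1.061, giving 3.71% × 1.061 = 3.94%.

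| g (h) | h = 2 h | h = 4 h | h = 8 h |
|---|---|---|---|
| 0 | 0 | 0 | 0 |
| 1 | 0.01% / 0.01% | 0.30% / 0.33% | 1.13% / 1.20% |
| 2 | 0.02% / 0.03% | 0.65% / 0.73% | 2.37% / 2.51% |
| 3 | 0.04% / 0.06% | 1.07% / 1.20% | 3.71% / 3.94% |

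Each cell shows the result without and then with the uptake phase. The denominator is the amount finally excreted in urine.

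**Step 3: comparison of the two administrations.** If one volunteer has g = 0 at one administration and g = 1 h at the other, the captured shares differ by about 0.3 percentage points at h = 4 h. The extreme of the assumed range, 0 against 3 h at h = 8 h, gives 3.9 points.

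**The case against.** **The gap may be negligible.** The Study Design puts a urine sample before the bolus but states no interval. The toxin is given in water, and nothing readable imposes a delay. A volunteer who drinks the bolus straight after the waking void satisfies both texts to within minutes. This stands: early stopping is conditional on g, and its size cannot be fixed from the protocol.

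**Part of the volunteer material is not visible.** The figure under the instructions heading, the study scheme and the timing flow diagram are not shown. The Methodology section also says the procedure is explained to each volunteer in detail. This stands too. A reader might infer that the bolus time was never recorded, but the documents do not support that; it may be in material not shown here. It would not remove the conflict, because the written end rule would still give less than 24 h for any g above zero.

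**The analysis origin is already the bolus.** A reader might infer that the waking time serves as time zero, so that the profile shifts by g and the time of peak excretion is badly wrong. The documents do not support that either: the analysis section counts hours after the bolus, and nothing uses the waking void as origin. No error in peak time is claimed here.

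**Pre-dose urine can be separated.** Each void has its own container, time and volume, so a void in the gap can be taken out once the bolus time is known. This stands.

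**The loss is small.** The top of the range needs a 3 h gap and an 8 h half-life together. This stands, and it sets the weight of the point.

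**Conclusion.** The conflict holds and is minor. The collection rule given to volunteers does not deliver the window the design states. It gives 24 − g hours after dosing, short of 24 h for any gap above zero.

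Under the assumed ranges the total loses from about zero to 3.9%, which would not change any conclusion about the 24-h amount by itself. What remains is local: hour 24 is incomplete or empty, and with a 3 h gap hours 22 to 24 are empty. Totals and late bins are also not strictly comparable if g differs between volunteers or between the DON and DON-3-glucoside administrations. A recorded bolus time lets every void be placed correctly, but it cannot recover the last g hours.

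The direction follows from the text alone. The size rests on assumed gaps, half-lives and first-order excretion.

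**What to change.** Reconcile the Urine Collection instructions with the Project summary, Study Design and analysis section, so that all use one time origin:

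- keep the waking void as the blank sample;
- make sure the clock time of the bolus is recorded, if the figures not shown do not already provide for it;
- treat any void between waking and bolus as pre-dose;
- set the last void at bolus time + 24 h;
- compute all post-dose times from the recorded bolus time.

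The cost is one changed paragraph and at most one field on the volunteer's schedule.

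The Duration of the Project section says that samples were collected from March to June, so new wording cannot change those collections. For them, report the post-bolus hours actually covered, by volunteer and by administration. Cutting every volunteer at the shortest common time would discard valid late urine to correct a loss of a few percent at most, so use it only as a sensitivity analysis. If the bolus time was not kept, say so as a limitation and give the plausible range of the gap. This costs a short table and one extra run of the totals.

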### **Data Management and Statistical Analysis**

**The protocol should provide information on how the data will be managed, including data handling and coding for computer analysis, monitoring and verification. The statistical methods proposed to be used for the analysis of data should be clearly outlined, including reasons for the sample size selected, power of the study, level of significance to be used, procedures for accounting for any missing or spurious data etc. For projects involving qualitative approaches, specify in sufficient detail how the data will be analysed.**

Firstly, we agree a coding system for the samples. The coding system is that all samples have two number separated by a "." where the first number is the volunteer id and the second number is the number of the sample of each volunteer. So the first urine sample of the volunteer 1 is 1.1 and the second sample of the volunteer 1 was 1.2. On the other hand, the second sample for the volunteer 2 is 2.1 and the second samples of the volunteer 2 is 2.2. We introduce an excel file all the information for each volunteer id.

Once we analyse the samples, the data of each sample is introduced in the same excel file and the results of each mycotoxin are introduced separately. Then, all obtained results are carried out on molar basis taking the molecular weight of the analytes (DON, 296 g/mole; DON-3-glucoside, 458 g/mole; DON-3-glucuronide and DON-15-glucuronide, 472 g/mole; DOM-1, 280 g/mole; 3-ADON and 15-ADON, 338 g/mole) and the total volume of each sampling point into account. Associations between independent and dependent variables are assessed by using univariate and multivariable linear regression models. Independent variables include age (years), gender, body mass index (BMI),

and the consumption of coffee. The statistical analysis is performed using the software Microsoft Excel® 2010 and SPSS® 15.0.

The excretion profiles are based in values obtained each hour after the bolus administration from a varying number of volunteers per time period. For instance, results from 61 to 120 minutes are clustered in the second hour.

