### **Study goals and objectives**

**Goals are broad statements of what the proposal hopes to accomplish. They create a setting for the proposal. Specific objectives are statements of the research question(s). Objectives should be simple (not complex), specific (not vague), and stated in advance (not after the research is done). After statement of the primary objective, secondary objectives may be mentioned.**

Due to the lack of information about DON absorption and excretion, the aims of this study are the description of the DON and metabolites excretions patterns and know the absorption and excretion rates of it. Moreover, the results can be useful to build an standardized method to estimate deoxynivalenol-intake by means of biomarkers.

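### The hourly excretion profile places each void in the post-bolus hour it was passed, with no correction for time since the previous void and a changing set of volunteers per hour

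*Protocol*

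**What the plan says.** Collection is void by void. Under Study Design, "From the moment of administration, the 24-hours urine sample collection is requested", and for every sample "time (hour of urine collection) and voided volume is recorded". The URINE COLLECTION instructions tell volunteers: "Always use another container per splash". They also require a final void at the end of the 24 hours, with an alarm set for it. On supplies, Study Design states: "We deliver to each volunteer 12 containers (1L) to collect the urine". No timed hourly voiding is asked for.

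Under Data Management and Statistical Analysis, results are converted to moles, taking the molecular weight "and the total volume of each sampling point into account". The value for a sample is thus the amount in the whole void. The same section builds the profile: "The excretion profiles are based in values obtained each hour after the bolus administration from a varying number of volunteers per time period". Its example is that "results from 61 to 120 minutes are clustered in the second hour". It gives no division by the interval since the previous void, no midpoint, no cumulative curve and no fixed denominator.

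The aims under Study goals and objectives are to describe the excretion patterns and to "know the absorption and excretion rates of it". Expected Outcomes of the Study adds that the speed of excretion should show whether a morning urine or a 24 h collection is preferable.

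**The concern.** The amount in a void is an integral over the time since the bladder was last emptied. Treating it as the excretion of the hour in which it was passed confuses an amount over an interval with an amount per hour. Voids after long gaps look like high excretion, and what was excreted early in a gap is shown late.

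If each hourly value is also a mean over only those who voided in that hour, non-voiders drop out although they were excreting too. Neighbouring points then describe different people.

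The profile serves the study's main aim. It also bears on the choice between morning and 24 h urine, and the void after the night is the one most exposed to this distortion.

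**Working it through.** The protocol gives no numerical profile or rate to reproduce, so the check is a count followed by a simulation of the stated rule.

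**1. Count.** Inputs from the protocol: 24 post-bolus hours, 12 containers, one void per container, 20 volunteers (16 dosed if the 4 controls are drawn from the 20).
- Hours without a void, per volunteer: at least 24 − 12 = 12.
- Contributors per hour, averaged over the 24 hours: at most 12/24 × 20 = 10 of 20, or 12/24 × 16 = 8 of 16.

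The set of contributors must therefore change from hour to hour.

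**2. One volunteer by hand.** Assumed kinetics (not in the protocol): one compartment, uptake ka = 1.5/h, half-life 4 h, so ke = ln 2/4 = 0.1733/h. Cumulative excretion as a share of recoverable dose is

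E(t) = 1 − [ka·exp(−ke·t) − ke·exp(−ka·t)]/(ka − ke).

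This gives E(2) = 20.7%, E(4) = 43.5%, E(5) = 52.5%, E(16) = 92.9% and E(24) = 98.2%.
- Voids at 2 h and 5 h: the second holds 52.5 − 20.7 = 31.8% and is placed in hour 5. True excretion in hour 5 is 52.5 − 43.5 = 9.0%. Divided by its 3 h interval, the void gives 10.6% per hour.
- Voids at 16 h and 24 h: the last holds 98.2 − 92.9 = 5.3% and is placed in hour 24. True excretion in hour 24 is 0.33%. Divided by 8 h, the void gives 0.66% per hour.

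**3. Simulation, 20 volunteers.** Assumptions: ka = 1.5/h; half-life 2, 3 or 6 h; 70% of dose recovered in urine; 6, 8 or 12 voids, all but the last within hours 0 to 16 and the last at 24 h. Each void's full amount goes into its hour and is averaged over those who voided in that hour. The true peak is in hour 2 throughout.

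| Voids | Median apparent peak (hour) | Sum of hourly means ÷ true 24 h excretion | Hour-24 value ÷ true | Volunteers per waking hour |
|---|---|---|---|---|
| 6 | 6 | 2.9–3.1 | 17–67 | 6.2 |
| 8 | 4–5 | 2.2–2.4 | 15–57 | 8.7 |
| 12 | 3 | 1.5 | 14–48 | 13 |

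A variant with a different random void pattern and about 12 voids gave a sum of 1.4. The range is therefore about 1.4 to 3.1.

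The inflation has a simple source. Dividing by the n volunteers who voided, instead of all N, multiplies each hour by N/n. In waking hours that is 20/13.1 = 1.5, 20/8.7 = 2.3 and 20/6.2 = 3.2, close to the third column. Void frequency drives the sum more than half-life does.

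**4. Same data, interval-adjusted.** Spreading each void evenly over the time since the previous one, with all volunteers in the denominator, gives hourly means that add up to the true 24 h excretion: 0.70, 0.70 and 0.65 of dose for half-lives 2, 3 and 6 h. The median peak falls in hour 2 or 3.

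**5. A rise at waking?** With 8 voids and none at night, hour 24 against hour 16 reads 0.7% against 1.1% of recoverable dose at half-life 2 h (no rise), and 12.7% against 7.1% at half-life 6 h (a rise). At half-life 4 h, with about 7 voids a day and half the volunteers voiding once at night, it reads 3.6% against 3.8% (no rise).

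**The case against.** The strongest reply is that the text is thin. It does not say whether the plotted value is an amount, a concentration, a rate or a percentage of dose, and it never mentions a mean. Averaging over voiders only is implied by the varying number of volunteers, not spelled out, and this stands as a limit on the reading. But the section does fix molar amounts from whole volumes and does fix assignment by hour of collection, so this is a stated rule and not a matter merely left open.

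A reader might infer that 24 h recovery is overstated by the same factor. The documents do not support that. Nothing in them adds hourly means to obtain recovery, and each volunteer's total is the sum of that volunteer's own voids. The ratios above only gauge how far the hourly values are inflated.

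A reader might also infer that all absorption and excretion rates in the study will be wrong. The protocol does not say that rates are taken from the hourly profile, so the bias reaches only rates that are.

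Nor does every profile under this rule show a second rise at waking, as step 5 shows. An empty night is itself an assumption, because the instructions cover collection by day and night.

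The peak shift should be kept in proportion. At half-life 4 h, true hourly excretion is 12.9%, 12.2% and 10.6% in hours 2, 3 and 4, so the true peak is fairly flat. Finally, the profile is descriptive, with no test or safety decision attached, and can be rebuilt from recorded data. That makes the repair easy, but it does not make the rule sound.

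**Conclusion.** The concern holds for the hourly profile, its peak time and any rate read from it. As written, the rule shows the peak late, inflates hourly values and inflates the 24 h void when it contains the night's urine. A later peak and inflated hourly values appeared in every setting tried.

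The size is conditional. It rests on uptake of 1.5/h, half-lives of 2 to 6 h, 6 to 12 voids, and averaging over voiders only, none of which the protocol states outright. On those assumptions the hourly means add up to about 1.4 to 3.1 times the true excretion, and the apparent peak falls in hours 3 to 6 instead of hour 2. Recovery over 24 h for each volunteer is sound. The rule should be replaced before the profile is used for the excretion-pattern aim or for the choice between morning and 24 h urine.

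**What to change.** Replace the clustering rule under Data Management and Statistical Analysis with one of these:
- For each void, compute nmol in the void divided by hours since the previous void (since the bolus for the first), and plot it at the interval midpoint or spread it over the interval.
- For each volunteer, build the cumulative percentage-of-dose curve and interpolate it to fixed times, for example 1, 2, … 24 h.

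Either is sufficient. In both, average over all dosed volunteers so that the denominator is constant, and state that number. Hourly grouping may stay once values are interval-adjusted. Also say what quantity is plotted and from which quantity any rate is derived.

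The cost is new analysis wording and a little more computation. Void times and volumes are already recorded, and the present rule already needs the bolus time, so no new data are required. One limit remains: timing within a void interval cannot be resolved, so a peak from the adjusted profile is only as precise as the gaps between voids.
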